### Outcomes measures

The primary outcomes of interest in this type 2 hybrid trial are 1) the effectiveness of the HOPE 2.0 intervention in increasing uptake of cervical screening among WLWH, and 2) the adoption of HOPE 2.0 intervention at the facility level. Other outcomes, including cost, fidelity, penetration, and sustainability, will be assessed as secondary outcomes. Additionally, Proctor et al.’s [61] client (i.e., WLWH) health outcomes will also be assessed (Fig. 2).*Cervical screening uptake* is defined as the proportion of WLWH in each study arm that successfully complete the cervical screening process. In the intervention arm, completing the process requires the WLWH to present to the clinic, collect a self-test kit, collect a cervical sample, and submit the sample to the clinic for testing. In the control arm, completing the process requires the WLWH to present to the clinic and receive a pap smear/cervical sample collection from a provider. WLWH in either study arm who do not complete the entire process will not be considered as completing uptake. Uptake assessment will therefore be determined as proportion of WLWH with complete screening out of all women enrolled in each study arm.*Program Adoption* is defined as the decision of healthcare workers (i.e., providers and management) and patients (described as patient uptake) to commit to and use HOPE 2.0 and ISS adoption. Adoption will be measured at provider, management, and patient levels using a variety of data logs, surveys, and interviews.At the management level, we will assess (i) the number of ISS training sessions attended and (ii) the degree to which ISS components are used to support providers.At the provider level, we will assess (i) the number of ISS training sessions attended, (ii) the degree to which ISS components are used, and (iii) the number of implementation plan steps followed. Additionally, we will assess providers’ (i) implementation experience (i.e., resource availability, managerial support, and technical issues confronted); and (ii) operational experience (i.e., workload increase or decrease, flow of health facility communication, and any skills needed).*Implementation Cost* is defined as the total expenses (facility/provider and patient) for implementing HOPE 2.0. Cost will be assessed at the health facility level in both study arms. We will use a micro-costing approach to estimate the economic costs associated with each study arm. The direct measure method of micro-costing involves tracking resources used and enumerating unit costs for each resource to precisely estimate cumulative costs associated with each study arm [62]. Implementation cost will be measured at the health facility level and patient level, utilizing a variety of cost-tracking databases throughout the study period to itemize, quantify, and value resources.At the health facility level, a cost-tracking database will be used throughout the study period to itemize, quantify, and value resources. Costs at the facility level include (i) number of hours staff spent on HOPE 2.0 training; (ii) sampling materials, including kits and laboratory testing costs; (iii) recruitment (i.e., time spent identifying and contacting eligible women, advertising materials, participant incentives); (iv) HOPE 2.0 delivery (with and without ISS); and (v) treatment and biopsies.Cost to the patient will include tracking of participant out-of-pocket costs (e.g., transportation, childcare, phone data, time spent on HOPE 2.0 procedures). French et al.’s outpatient cost survey [63] (5 items) will be adapted to measure patient-level costs.Note: Time effort will be estimated using the hourly wages of WLWH and healthcare workers.*Fidelity* is the degree to which HOPE 2.0 and its ISS are implemented as planned.At the provider level, utilizing surveys, log sheets, and interviews, we will assess (i) the degree of adherence to HOPE 2.0/ISS protocols (Intervention) and HOPE 2.0 (Control) during implementation, (ii) the dose of the program delivered, and (iii) the quality of program delivery.At the management level, we will assess (i) adherence to ISS protocol (Intervention only) and (ii) overall management support for providers (both arms).We will utilize log sheets and interviews, as well as observations, and the Process Evaluation Checklist (PEC) [64] throughout to track the fidelity of implementation and overall project progress.*Program Penetration* for this proposal is the integration of HOPE 2.0/ISS within the HIV subsystem of study facility settings [61]. We will assess penetration outcomes at provider and management levels by determining the proportion of personnel who actually deliver on a HOPE 2.0 program task/role, out of the number trained or expected to deliver on that task/role.At the management level, we will utilize log sheets and interviews to measure the expected tasks or roles to be evaluated, which will be (i) the provision of technical support and (ii) facilitating a conducive HOPE 2.0 implementation climate for providers.At the provider level, we will utilize log sheets and interviews to measure the expected tasks to be evaluated, which are (i) screening and recruitment of eligible WLWH, (ii) delivery of HOPE 2.0 to enrolled WLWH, and (iii) follow-up on all testing outcomes and completion of required documentation for these tasks/roles.*Program Effectiveness* is defined as the impact of the ISS on 1) providers' self-efficacy in implementing HOPE 2.0, 2) WLWH screening uptake, and 3) treatment outcome. We will assess effectiveness outcomes at management, provider, and WLWH levels utilizing surveys, log sheets, and interviews.At the management level, we will assess (i) the frequency of support that management delivers to providers, (ii) management self-efficacy in supporting HOPE 2.0 implementation, and (iii) challenges in supporting HOPE 2.0 implementation at their facilities, utilizing log sheets and interviews.At the provider level, we will assess (i) self-efficacy for implementing HOPE, (ii) fidelity of HOPE 2.0 intervention delivery, (iii) number of WLWH screened and women with positive results who are treated, and (iv) the type, frequency, duration, and quality of service provided to patients (WLWH).At the WLWH level, we will assess the impact of HOPE 2.0 on patients’ (WLWH) screening uptake (i.e., service outcome) and receipt of screening results, patient satisfaction, and for women with positive screening results, clinical follow-up, and evaluation for, and receipt of CC treatment where appropriate (i.e., client outcomes). Assessment procedures: WLWH in both study arms will complete the screening and satisfaction outcome survey within one month of completing HOPE 2.0. Within one month of screening, providers will check the lab registry and will review the electronic medical record to confirm screening completion. Treatment compliance will be evaluated within 6 months of positive result notification. The screening and treatment completion outcomes will be binary (yes/no), test results (positive, negative, or inadequate), treatment follow-up (yes, no, or lost-to-follow-up), and patient satisfaction will be measured using a patient satisfaction survey [65].

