#### Evidence-based patient navigator support

Patient navigators, trained lay or volunteer health workers, play a vital role in improving equitable access to, and sustained use of HPVSS [37]. In Ghana, they routinely deliver health education and community-based services for various conditions, including breast cancer and HIV [44]. Within the HOPE intervention, patient navigators motivated WLWH, facilitated questionnaire completion, addressed participant questions, and ensured timely distribution and return of HPVSS kits. These activities enhanced service uptake, improved screening rates, and reduced diagnostic delays, consistent with findings from other LMICs [23, 45, 46].

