### Study procedures

#### Intervention arm

Step 1. Providers, i.e., clinicians, patient navigators, and clinic management at intervention sites will receive a) ISS delivered through management support, capacity-building, and social network support, and b) baseline and refresher training on the HOPE implementation plan.Step 2. Clinicians will a) screen and recruit eligible WLWH, and b) implement HOPE 2.0 by delivering 3R messages via WhatsApp to enroll WLWH.Step 3: WLWH will receive a self-sampling kit from clinicians or patient navigators to collect samples.Step 4: WLWH with positive screening tests will follow up for treatment per the WHO screen, triage, and treat cascade (Fig. 4). Patient navigators will support participants to follow up.

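### The uptake rule makes a clinic visit compulsory in the intervention arm, so a laboratory-tested self-sample can be scored as unscreened; the net bias in the effect has no known direction

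*Protocol article*

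**What the plan says.** Screening uptake is the first of the two primary outcomes under Outcomes measures. For the intervention arm the article states: "In the intervention arm, completing the process requires the WLWH to present to the clinic, collect a self-test kit"; she must then take a sample and submit it to the clinic. For the control arm, completing the process "requires the WLWH to present to the clinic and receive a pap smear/cervical sample collection from a provider". Scoring is all-or-nothing: "WLWH in either study arm who do not complete the entire process will not be considered as completing uptake". The measure is the "proportion of WLWH with complete screening out of all women enrolled in each study arm". For verification, "providers will check the lab registry and will review the electronic medical record to confirm screening completion".

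Other sections describe delivery differently:

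- The title and the Background call the intervention home-based self-sampling.
- Study procedures, Intervention arm, Step 3: "WLWH will receive a self-sampling kit from clinicians or patient navigators to collect samples". No place is named.
- The section on patient navigator support says that navigators in HOPE "ensured timely distribution and return of HPVSS kits". The Background says HOPE-inG keeps HOPE's three core components, navigator support among them.
- The Control arm section has control sites follow Steps 2 to 4 without navigator support, and the Implementation phase Design section says control women also receive HOPE. The Implementation phase hypothesis compares uptake by self-sampling between the arms.

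**The concern.** The scientific event is that a woman has been screened. The rule instead scores a pathway, and one step of that pathway, presenting to the clinic, is something home-based self-sampling could make unnecessary. If an intervention woman receives her kit away from the clinic, samples herself and has the sample returned for her, the laboratory has tested her but the written rule records no uptake.

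A co-primary outcome would then depend on the route as well as on screening. Sites could also diverge: one might apply the wording literally while another accepts any laboratory result. With two sites per arm, a difference in scoring practice between sites cannot be separated from a treatment effect.

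The control rule in the same paragraph has a route dependence of its own. It recognises only samples taken by a provider, although control women are meant to self-sample.

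**Working it through.** **1. The passages side by side.** Of the intervention-arm steps, presenting to the clinic is the one that conflicts with the described delivery. The rule does not say that the kit must be collected at the clinic, that sampling must happen there, or that the woman must return the sample herself. The literal misclassification therefore concerns women who never present to the clinic but whose sample is tested.

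**2. Inputs.** The protocol gives no figure for this misclassification, so there is none to reproduce. For scale:

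- Rates of 30% (intervention) and 15% (control), from Sample size estimation. They are stated for adoption; using them for uptake is an assumption. The Outcomes measures section does describe patient-level adoption as patient uptake.
- h = share of intervention completers who never present to the clinic. Not in the documents; varied.
- s = share of control completers who self-sample. Not in the documents; varied.

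**3. Formulas, with both rules applied literally.**

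- Scored intervention uptake = 0.30 × (1 − h)
- Scored control uptake = 0.15 × (1 − s)
- Scored difference = 0.30 × (1 − h) − 0.15 × (1 − s); true difference = 0.30 − 0.15 = 15 points

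**4. Scored difference in percentage points.**

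| h | s = 0 | s = 0.25 | s = 0.5 | s = 1 |
|---|---|---|---|---|
| 0 | 15 | 18.75 | 22.5 | 30 |
| 0.1 | 12 | 15.75 | 19.5 | 27 |
| 0.2 | 9 | 12.75 | 16.5 | 24 |
| 0.3 | 6 | 9.75 | 13.5 | 21 |
| 0.5 | 0 | 3.75 | 7.5 | 15 |
| 0.6 | −3 | 0.75 | 4.5 | 12 |

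Example: h = 0.2, s = 1 gives 0.30 × 0.8 − 0.15 × 0 = 0.24.

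**5. Direction.** The difference is understated when 0.30h > 0.15s, that is, when h > s/2. If every control completer self-samples (s = 1), more than half of intervention completers must bypass the clinic before the effect is understated.

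**6. In women.** With 576 per arm, 0.30 × 576 ≈ 173 intervention completers; at h = 0.2 about 0.2 × 173 ≈ 35 of them would be scored as unscreened.

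**7. Would copying the intervention wording to both arms cure it?** No. Control self-samplers would then count, but the clinic-visit condition would stay. Navigator support is confined to the intervention arm, so a navigator route around the clinic exists only there. If no control woman bypasses the clinic, the s = 0 column applies and any h above zero understates the effect.

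**The case against.** The strongest reply is that the home route is inferred. The article nowhere says that navigators take kits to women's homes in this trial. The section on outer and inner contexts lists navigators among supporting staff of the clinic setting, and a navigator handing over a kit at the clinic satisfies the rule. The sentence on kit distribution and return describes the earlier HOPE intervention and names no place. Phone contact and WhatsApp messages concern recruitment and education. All of this stands: h may be small or zero, and the documents cannot settle it.

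A second reply is that completion is confirmed from the laboratory registry and medical record. Neither is said to record where the kit was received, so a woman with a result would probably be marked complete. That is plausible, but it means relying on staff to disregard the written definition. It supports rewriting the definition to match the check.

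A reader might infer that the rule makes the trial understate its effect, and more so the better the home route works. The documents do not support this. It treats the control rule as free of error, whereas that rule, read just as literally, removes control self-samplers and pushes the difference upward. Nor do they support reading the rule as requiring that the kit be collected at the clinic or that the sample be returned in person.

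**Conclusion.** The definition is wrong as written. A co-primary outcome carries a compulsory clinic-visit condition that does not fit the home-based label, the navigator supply of kits in Step 3 or the navigators' role in HOPE, and it can score a tested woman as unscreened. Measured intervention uptake falls by the fraction h: from 30% to 27% at h = 0.1, 24% at h = 0.2 and 15% at h = 0.5.

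The net bias in the between-arm effect is of unknown direction. Over the ranges shown, a true 15-point difference could be scored anywhere from −3 to 30 points. These figures rest on three assumptions: the adoption rates are borrowed for uptake, h and s are not in the documents, and both rules are applied literally. They show sensitivity and are not a forecast.

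The inconsistency itself needs none of these assumptions. It should be corrected before outcomes are scored; the article says the Implementation Phase is only beginning and recruitment is ongoing.

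**What to change.** Replace the two arm-specific pathways with one event for both arms: an enrolled woman has uptake if a cervical or vaginal sample from her is logged in the laboratory registry, regardless of where the kit was obtained, where or by whom the sample was taken, or who returned it. Keep all enrolled women in the arm as the denominator. Delete the clinic-presentation and kit-collection steps from the scoring rule. Record kit source, place of sampling, collector and return route as descriptive variables, so that self-sampled uptake can also be reported separately.

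Reconcile the control-arm outcome text with the Implementation phase hypothesis, the Design section and the Control arm procedures. How control women are to be sampled is for the investigators to state; the event above works under either description.

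The cost is a sentence or two in the outcome definition and a few route fields on the log sheets. The laboratory registry check is already planned, and neither the sample size nor the randomization changes.

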### Implementation phase

Assess the effectiveness of the HOPE 2.0 intervention and the success of the implementation plan in a hybrid type 2 trial.

*Hypothesis: Cervical screening uptake by HPVSS will be significantly higher among WLWH in the intervention vs. the control group, and implementation outcomes scores among intervention group providers will be significantly higher than those of control group providers.*

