#### Design

We will conduct a hybrid type 2 cluster randomized controlled trial to simultaneously evaluate the effectiveness and implementation of HOPE 2.0 using bridging factor-focused ISS. HIV clinics at the four selected secondary-level facilities will be cluster randomized 1:1 in a two-arm trial. WLWH in the intervention group will receive HOPE 2.0 from providers trained and supported to implement HOPE 2.0 using ISS-focused training materials and per the implementation plan developed in the Preparation Phase. After this intensive 6 month implementation phase, technical and clinical support from the study team and clinical experts to the intervention sites will be withdrawn, after which the Sustainment Phase will begin

WLWH in the control group will also receive HOPE, from providers without ISS or an implementation plan (Table 2 and Fig. 2). At the end of this 6 months period of implementation, the study team will provide ISS materials to control group health facilities to co-implement with HOPE 2.0. There will be a similar Sustainment Phase for the control sites.

**Table 2 Tab2:** HOPE-inG baseline provider training in intervention vs control arms

	**Topic**	**Intervention Arm**	**Control Arm**
1	Epidemiology of cervical cancer (CC) in women with and without HIV	Yes	Yes
2	The WHO cervical cancer elimination agenda	Yes	Yes
3	The HOPE intervention: components and evidence	Yes	Yes
4	Cervical cancer screening strategies	Yes	Yes
5	Pre- and post cervical screening counselling	Yes	Yes
6	Psycho-social support for clients with positive cervical screening results and their immediate family	Yes	Yes
7	Awareness creation, record keeping and documentation	Yes	Yes
8	Research ethics: participant recruitment, study procedures and collecting, documenting and reporting data	Yes	Yes
9	Delivering the HOPE intervention in Ghana: Implementation research to practice	Yes	No
10	Who is supposed to do what, where and when? The HOPE 2.0 implementation plan	Yes	No
11	How will we deliver the intervention? Implementation support strategies for HOPE 2.0	Yes	No
12	What resources do we have for successful implementation? Additional tools, job aids, support and training for delivering HOPE 2.0	Yes	No

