#### Recruitment

*Doctors, nurses, patient navigators, and clinic managers:* We will meet with Medical Directors of the selected health facilities to discuss the study and the recruitment of providers. We will recruit providers by email, phone, and face-to-face contact.*WLWH* will be recruited using E-tracker electronic records. Participating providers at each site will identify eligible women from their site-level sampling frame (400–600 per site for a total pool of ~ 3,900 WLWH) and contact them by phone to solicit participation. Verbal informed consent will be sought in English/applicable local language by research coordinators prior to trial initiation. Participant recruitment is ongoing and will be completed by March 2028.*Community members* will be recruited from study communities via community gatekeepers.Ghana Health Service and the Ministry of Health will facilitate the recruitment of government officials through written and verbal invitations and snowball recruitment.

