#### Control arm

Providers and clinic managers at control sites will receive baseline training on study implementation, but will not receive any ISS or implementation plan training (Table 2). They will, however, be required to follow Steps 2, 3, and 4 described in the intervention arm described above, except for patient navigator support.

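### Screening uptake, the first primary outcome, is scored on different events in the two arms, and the control rule contradicts the sections that give control women the self-sampling kit

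*Protocol article*

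**What the plan says.** The section Outcomes measures names screening uptake as the first primary outcome and gives each arm its own completion rule.

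- Intervention arm: "completing the process requires the WLWH to present to the clinic, collect a self-test kit, collect a cervical sample, and submit the sample".
- Control arm: "completing the process requires the WLWH to present to the clinic and receive a pap smear/cervical sample collection from a provider".
- Both arms: "WLWH in either study arm who do not complete the entire process will not be considered as completing uptake".
- The result is the "proportion of WLWH with complete screening out of all women enrolled in each study arm".

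Other sections describe a control arm that self-samples.

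- The Methods part of the Abstract sets HOPE 2.0 with ISS against HOPE 2.0 without it. The section The HOPE intervention lists the self-sampling kit as one of HOPE's three components.
- Design (Implementation phase): "WLWH in the control group will also receive HOPE, from providers without ISS or an implementation plan".
- Control arm: providers and managers will "be required to follow Steps 2, 3, and 4 described in the intervention arm", with navigator support excepted. Step 3 in the section Intervention arm is the handing over of the self-sampling kit.
- The hypothesis of the Implementation phase: "Cervical screening uptake by HPVSS will be significantly higher among WLWH in the intervention vs. the control group".

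No sentence lets a self-collected sample count as uptake in the control arm.

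**The concern.** A comparison of proportions between arms is meaningful only if the same event is counted in both. Here the counted event changes with the arm. The event counted for controls is also not the one that the procedures direct control women towards, nor the one named in the hypothesis.

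At stake is the first of two primary outcomes. Outcomes measures defines program effectiveness as what ISS does to, among other things, women's screening uptake. If the rule is applied as printed, a gap between arms may reflect how samples were collected and scored and not what ISS achieved.

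**Working it through.** **Two readings of the control arm.**

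*Reading A: control women receive the kit* (Abstract, The HOPE intervention, Design, Control arm with Step 3). A control woman who takes the kit, samples herself and returns it has done what the procedures ask. She has not had a sample taken by a provider, so the control rule scores her as no uptake.

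*Reading B: control women are sampled by a provider only* (Outcomes measures). The control rule then fits the care given, but the other sections are wrong. The arms differ in collection mode as well as in ISS. The hypothesis about self-sampling uptake then has almost nothing to count in the control arm.

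**Size under reading A.** Let p be the true completion rate by any mode, equal in both arms (no ISS effect). Let s be the share of control completers who self-sample, and t the share of intervention completers sampled by a provider, who are also excluded by their arm's rule.

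- Scored intervention rate: p(1 − t)
- Scored control rate: p(1 − s)
- Scored difference: p(s − t), which is p × s when t = 0

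The documents give no value for p, s or t, so these are assumptions shown over a range, with t = 0:

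| p | s | Intervention scored | Control scored | Difference (points) |
|---|---|---|---|---|
| 30% | 25% | 30% | 22.5% | 7.5 |
| 30% | 50% | 30% | 15% | 15 |
| 30% | 100% | 30% | 0% | 30 |
| 15% | 50% | 15% | 7.5% | 7.5 |
| 70% | 50% | 70% | 35% | 35 |

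With t = 10%, p = 30% and s = 50%, the difference falls to 0.30 × (0.50 − 0.10) = 12 points. Under one common rule it is p − p = 0.

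**The plan's own benchmark.** Sample size estimation plans for a rise from 15% to 30%, that is 15 points, and Table 3 gives 240 for that pair. Before clustering, (1.960 + 0.842)² × (0.30 × 0.70 + 0.15 × 0.85) / 0.15² = 117.7 per arm. No intracluster correlation (ICC) is stated for binary outcomes, so 240 cannot be derived from the stated inputs alone. With the stated coefficient of variation of 0.2, an assumed mean cluster size of 500 (the middle of the stated 400 to 600) and an assumed ICC of 0.002, the design effect is 1 + (1.04 × 500 − 1) × 0.002 = 2.038, and 117.7 × 2.038 rounds to 240. This formula yields a number per arm, whereas Table 3 is labelled per site. That is a separate matter, and the scoring argument does not depend on it.

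**Chance of a significant result with no ISS effect.** Inputs: 480 women per arm (2 × 240), two-sided α = 0.05, p = 30%, t = 0, design effect 1 + (1.04 × 240 − 1) × ICC, which is 1, 1.497, 3.486 and 13.43 for the four assumed ICCs.

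| s | ICC 0 | ICC 0.002 | ICC 0.01 | ICC 0.05 |
|---|---|---|---|---|
| 25% | 0.75 | 0.58 | 0.29 | 0.11 |
| 50% | 1.00 | 0.996 | 0.85 | 0.33 |
| 100% | 1.00 | 1.00 | 1.00 | 0.96 |

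The nominal rate in that direction is 0.025. The normal approximation ignores how few degrees of freedom four clusters leave, so these chances are illustrative only.

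**The case against.** The strongest objection is that the control sentence may be a leftover. Outcomes measures first defines uptake, neutrally as to mode, as successful completion of screening. It records completion as yes or no, has providers confirm it from the laboratory registry and electronic record, and surveys women in both arms after they complete HOPE 2.0. An analyst might sensibly count any completed screen. That is plausible, but the arm-specific rules are printed and explicit, and the registry check only confirms a completion that those rules define. The intent-to-treat statement keeps women in their assigned arm; it does not make the scoring equal. Nor is this a detail left to an analysis plan, because the article states the rule and contradicts it.

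A reader might infer that the trial is bound to show a false benefit. The documents do not support that. They conflict, and either side may be the error. The artefact in favour of the intervention needs reading A, literal scoring and s greater than t. The 15-point benchmark is also stated for implementation outcomes such as adoption, not expressly for screening uptake.

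A reader might also see a conflict between the intervention rule's clinic attendance and Step 3, where navigators may hand out kits. None is shown: Step 3 does not say that kits are given off site, and the section on outer and inner contexts lists navigators as clinic support staff. How women are identified and contacted for recruitment is a separate question and adds nothing to this one.

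**Conclusion.** The point stands and should be corrected before uptake is analysed. It is certain from the text that the two arms have different completion events, and that the control event conflicts with the Abstract, the hypothesis, Design and Control arm. Under reading A the scored difference is p(s − t) with no ISS effect: 7.5 to 30 points at an assumed p of 30%, t of zero and s from 25% to 100%. Under reading B no such artefact need arise, but a difference would mix collection mode with ISS and could not be attributed to ISS. The sizes rest on assumed p, s and t, and the rejection chances also on an assumed ICC; the inconsistency itself rests on none of these.

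**What to change.** 1. Reconcile the Abstract, the hypothesis, Design, Intervention arm (Step 3), Control arm and Outcomes measures on how control women are screened. Which description is right is for the sponsor to state.
2. Replace the two arm-specific rules with one: a cervical screening sample received for testing, confirmed in the laboratory registry, within the same window counted from enrolment in both arms. The present registry check is timed from screening, a date that unscreened women do not have.
3. Report collection mode by arm. To match the hypothesis, also report uptake by self-sampling alone, scored identically in both arms.

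The cost is a protocol amendment to the wording and a fixed window; the registry check is already planned, and the Discussion places the trial at the start of its Implementation phase. The change has a limit. A common rule makes the scoring fair but does not by itself isolate ISS, because Control arm also withholds navigator support. If reading B proves to be the actual care, the difference in collection mode remains and the stated contrast has to be reworded.
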